### Statistical methods

#### Quantitative data analysis

Quantitative data will be analysed using SPSS version 22.0 for Windows (SPSS Inc., Chicago, IL) employing an intention-to-treat analysis (based on their treatment allocation and irrespective of participants’ adherence or withdrawal) [68]. The level of significance will be set at *p* < .05; however, any hypothesis testing is preliminary and results will be interpreted with caution as this pilot study is underpowered and the analyses based on small numbers. Baseline differences between groups for continuous data (e.g. age, BMI, resting blood pressure, number of comorbidities, cognitive and physical functioning, and outcomes of questionnaires) will be analysed using one-way ANOVA. Chi-squared tests will be applied for nominal data (e.g. gender, ethnicity, marital status, living arrangements, level of education, children and employment status). For descriptive statistics, data will be presented as means (M) and standard deviations (SD). Nominal data will be presented as number (*N*) and percentage. Mixed between (group) and within (time) repeated-measures ANOVAs with post-hoc comparisons will be applied to investigate the effect of the intervention versus control on psychosocial outcomes (loneliness, social support, support networks, depression, anxiety, self-efficacy for exercise, satisfaction with level of social contacts), expected outcomes and barriers for exercise, and accelerometer data. The accelerometer data will be analysed using the ActivPAL software V7.1.18 (PAL technologies, Scotland, UK). Recorded data will be downloaded to a computer, and data for average daily amount of stepping (step counts), average time lying and sitting (h) in increments of 15 s, average time standing (h) and energy expenditure (EE, MET/h) will be analysed using mixed between (intervention group) and within (time) ANOVAs. For the Expected Outcomes and Barriers for Habitual Exercise scale [58], additional test-retest reliability will be calculated via correlation. In order to explore which outcome measures are likely to be the most important for the main trial, Pearson’s correlations will be performed between calculated change scores over time in the experimental group for all psychosocial outcomes (Lubben’s social networks, loneliness and self-efficacy for exercise) and change scores for averaged daily physical activity (time lying/sitting (h), time standing (h), time stepping (h), step counts, sit-to-stand transitions (n) and energy equivalent (METs/h)). A power calculation and sample size estimation for a future large-scale RCT will be calculated for meaningful outcomes (e.g. loneliness or social support) using the method based on the differences in means between the intervention and control group using the G-power software Version 3.1 [62].

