## Methods/design

PAIL is a tw0-arm RCT of a 12-week intervention compared with a wait-list control (WLC) condition using a mixed-methods research design (including quantitative and qualitative research methods). Quantitative data will be collected from the intervention and control groups at the baseline and immediate post-intervention periods. Qualitative data aimed to assess the appropriateness, practicality and acceptability of the designed intervention in the proposed settings will be collected at the mid-point and post-intervention period. The trial was approved by the Science, Technology, Engineering and Mathematics (STEM) Research Ethics Committee of the University of Birmingham, UK (ERN_16-1419A). Consent forms (Additional file 1) will be obtained from all participants prior to entry into the study. This protocol for a feasibility study was guided by the SPIRIT 2013 Checklist (Additional file 2).

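### The two-time-point repeated-measures ANOVA is a change-score test; adjusting follow-up for baseline (ANCOVA) would give a more precise effect estimate that chance imbalance does not shift

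*Protocol article*

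**What the plan says.** The section Quantitative data analysis fixes one model for the psychosocial and accelerometer outcomes: "Mixed between (group) and within (time) repeated-measures ANOVAs with post-hoc comparisons will be applied to investigate the effect of the intervention versus control". The section Feasibility outcomes names the same model as the source of the effect size for change in loneliness. Neither section mentions a baseline-adjusted model or says which term or contrast is the treatment effect.

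There are two measurement times. Methods/design states: "Quantitative data will be collected from the intervention and control groups at the baseline and immediate post-intervention periods". Sample size gives 20 participants per arm.

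The analysis section also plans significance tests of "Baseline differences between groups for continuous data" and of nominal variables, with no adjustment tied to the results. It describes the analysis as "employing an intention-to-treat analysis (based on their treatment allocation and irrespective of participants’ adherence or withdrawal", and says that "any hypothesis testing is preliminary and results will be interpreted with caution as this pilot study is underpowered". A sample-size calculation for the future trial, based on differences in means between the groups, is to follow.

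**The concern.** A mixed ANOVA with two groups and two times offers several readings of the treatment effect: the interaction, the group main effect, or a post-hoc contrast. The natural one is the interaction, which compares mean change between arms. A change score gives baseline a fixed weight of one. The best linear weight, with equal SDs at both times, is the baseline-to-follow-up correlation, which is below one. The change score therefore carries avoidable noise, and if one arm happens to start higher it subtracts too much.

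This matters because Study objectives lists the future trial's sample size and the suitability of the statistical methods among the study's aims, and adds the between-group effect sizes. The estimates handed on would be noisier than the collected data require. With 20 per arm they would also depend more than necessary on the luck of the baseline draw.

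**Working it through.** **Inputs from the article.** Two measurement times (Methods/design); 20 per arm, 40 in total (Sample size); at least 75% retention per group (Progression criteria). The figure of 40 has no effect size, SD or power behind it. The only check available is the sum: 20 + 20 = 40, and 10 a month × 4 months = 40.

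**Assumptions.** The article gives no correlation ρ between baseline and follow-up, so 0.4 to 0.8 is assumed. Equal SDs at both times are assumed, and results are in units of that SD.

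**Step 1: what the interaction tests.** With two times, the group-by-time F equals the squared t statistic on change scores. A numerical check on simulated data gave 0.002427 for both.

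**Step 2: precision.** Per-person variance is 2(1−ρ) for the change score and 1−ρ² for ANCOVA, so the ratio is (1−ρ²)/[2(1−ρ)] = (1+ρ)/2. Estimating the covariate slope costs a factor of about 1 + 1/(N−4) = 1 + 1/36 = 1.028 at N = 40.

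**Step 3: imbalance.** The standard error of the baseline difference is √(2/20) = 0.316 SD. Given an imbalance of that size, the expected shift is (ρ−1) × 0.316 in the change-score estimate and 0 in the ANCOVA estimate.

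| ρ | Change score 2(1−ρ) | ANCOVA 1−ρ² | Ratio (1+ρ)/2 | Ratio × 1.028 | Variance reduction | Change-score shift (SD) |
|---|---|---|---|---|---|---|
| 0.4 | 1.20 | 0.84 | 0.70 | 0.719 | 28% | −0.19 |
| 0.6 | 0.80 | 0.64 | 0.80 | 0.822 | 18% | −0.13 |
| 0.8 | 0.40 | 0.36 | 0.90 | 0.925 | 7.5% | −0.06 |

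Analysing follow-up alone has variance 1. Below ρ = 0.5 the change score, with 2(1−ρ) > 1, is thus less precise than ignoring baseline altogether.

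At ρ = 0.6 the standard error of the effect is √(0.1 × 0.80) = 0.28 SD as planned and √(0.1 × 0.64 × 1.028) = 0.26 SD with ANCOVA.

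**Step 4: simulated power** (20,000 runs, 20 per arm, assumed true effect 0.5 SD, two-sided 5%). Interaction against ANCOVA: 33.6% against 41.8% at ρ = 0.5, and 50.9% against 56.5% at ρ = 0.7.

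**Step 5: why the term must be named.** The group main effect averages baseline with follow-up, so it estimates only half the effect. In the same simulations its power was 14.3% (ρ = 0.5) and 13.3% (ρ = 0.7). A baseline imbalance of 0.316 SD shifts it by (1+ρ)/2 × 0.316, which is +0.24 and +0.27 SD.

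**Step 6: does the change rescue participants without follow-up?** Randomisation follows the baseline measures (Randomisation and concealment), so a person who withdraws typically has a baseline and no follow-up. At 75% retention that is 10 of 40. Complete-case ANCOVA omits them. A mixed model with a common baseline mean includes their baseline, but its likelihood factors into the baseline distribution and the regression of follow-up on baseline and group. The group effect sits only in the second factor, to which only people with follow-up contribute. Neither analysis gains information on the effect from those who withdrew.

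**The case against.** The strongest defence is that little depends on this choice. The article calls its testing preliminary and the study underpowered, Progression criteria use only safety, recruitment and retention, and effect sizes are listed as an addition to the main aims. An estimate with a standard error of 0.26 SD is still very imprecise, and 40 participants limit the future sample-size calculation far more than the choice between change score and ANCOVA does. All of this stands and keeps the point modest. It does not justify giving up precision when the baseline is already collected.

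A reader might go further in four ways that the article does not support.

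- **The plan wastes the baseline and leaves imbalance uncorrected.** The interaction does use baseline, and it over-corrects. Imbalance would remain only if the group main effect or a comparison of follow-up means were read as the effect, and the article does not say so.
- **Withdrawals are deleted, contradicting intention to treat.** A standard repeated-measures ANOVA does need both measurements, but the article gives no rule for missing follow-up. Imputation before the ANOVA would fit its wording, and such a rule may stand in the SAP or full protocol, which are not shown.
- **The post-hoc comparisons are within-arm.** The article says only that they are post-hoc, and gives the purpose as intervention versus control. Reading a within-arm change as an effect is a risk to guard against, not something planned.
- **The planned estimate is biased.** Over repeated randomisations it is unbiased. The shift is conditional on the imbalance that happens to occur.

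**Conclusion.** The point holds as one of efficiency and clarity. As a change-score test, the planned interaction has a larger variance than ANCOVA. Switching lowers the variance by roughly 7% to 28% at N = 40 for ρ between 0.8 and 0.4, and the gain shrinks as ρ rises. A one-standard-error baseline imbalance shifts the planned estimate by 0.06 to 0.19 SD in the opposite direction over the same range, and leaves ANCOVA unmoved. The term that carries the treatment effect is not named, and reading the wrong one would cost much more than the change score does.

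These sizes rest on an assumed ρ, equal SDs at both times, and a common linear relation between baseline and follow-up in the two arms. The finding does not show that the intention-to-treat statement is breached, and the remedy does not by itself fulfil that statement.

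**What to change.** In Quantitative data analysis, and to match in Feasibility outcomes, replace the mixed ANOVA: for each outcome, regress the follow-up score on group with the baseline score as covariate. Name the adjusted between-group mean difference, with its 95% confidence interval, as the effect estimate that goes into the future sample-size calculation. State that within-arm changes are not read as the intervention effect. Present baseline data descriptively in place of significance tests, since under randomisation any baseline difference between arms is due to chance.

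Do not present the change as a treatment of missing follow-up. How the intention-to-treat statement is met for people without a second measurement is a separate matter that ANCOVA does not settle.

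The cost is a wording change and one extra estimated coefficient per outcome. The data and software stay the same.

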#### WLC group

Participants in the wait-list control (delayed intervention) group will start the intervention after their follow-up measures are completed approximately 12 weeks post-randomisation.

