### Measures

All measures will be conducted at the host academic institution at baseline and at the immediate post-intervention period (Fig. 1) except for focus groups, which will take place at the mid-point and post-intervention.

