#### Questionnaires

*Loneliness* will be assessed using the 8-item UCLA Loneliness Scale (UCLA-8) [52]. *Social support* will be assessed using the 20-item Medical Outcomes Study Social Support Survey (MOSSSS) [53]. *Social networks* will be assessed using the 6-item Lubben’s Social Network Scale (LSNS-6) [54]. *Depression and anxiety* will be assessed using the 14-item Hospital Anxiety and Depression Scale (HADS) [55]. *Self-efficacy for exercise* will be measured using the revised 9-item Self-Efficacy for Walking/Exercise Scale (SEE) using a paper-and-pencil format [56]. *Satisfaction with level of social contacts* will be measured with the question “How satisfied are you with your social contacts?” [57]. *Expected outcomes and barriers for exercise* will be administered using the Expected Outcomes and Barriers for Habitual Exercise scale [58] adapted for the older adult population. Four questions related to sport competence have been deleted from the expected outcomes sub-scale due to irrelevance for this population group [58]. The expected outcomes and barriers for exercise scale have demonstrated good internal consistency from 0.66 to 0.85 and a high test-retest reliability of 0.78 in previous research [58].

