### Data collection

Data will be collected at the university facility at screening, baseline and post-intervention period (12 weeks after the start of the intervention) (Fig. 1). After providing baseline eligibility screening, potential participants will be offered a total of five visits for health assessments at the university facility. Participants in the intervention group will have an additional sixth visit for attending the mid-point focus group. All digital data (transcripts, digital information, health assessment databases) will be stored securely on the password-protected university computers available only to the research team. All other data (e.g. eligibility screening forms, activity data and questionnaire data) will be pseudo-anonymised with a unique ID number and stored in locked filing cabinets/on password-protected university computers accessible only to the research team. Only the researchers will have access to the data.

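### Test-retest reliability of the adapted exercise outcomes and barriers scale is planned without excluding the treated arm, so the coefficient can mix measurement error with response to PAIL (minor)

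*Protocol article*

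**What the plan says.** The Quantitative data analysis section states, for the Expected Outcomes and Barriers scale, that "additional test-retest reliability will be calculated via correlation". It names no time points, arm or type of coefficient.

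On when the scale is given, the Measures section says "All measures will be conducted at the host academic institution at baseline and at the immediate post-intervention period", with focus groups as the only exception. Data collection places the second occasion at the "post-intervention period (12 weeks after the start of the intervention".

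The scale is also an outcome. The list of variables for the group-by-time repeated-measures ANOVA includes "expected outcomes and barriers for exercise, and accelerometer data".

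Under Questionnaires the article reports that "Four questions related to sport competence have been deleted from the expected outcomes sub-scale due to irrelevance for this population group", and cites "a high test-retest reliability of 0.78 in previous research".

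For the controls, the WLC group section says that the wait-list "group will start the intervention after their follow-up measures are completed approximately 12 weeks post-randomisation".

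**The concern.** Test-retest reliability asks how closely two scores agree when the thing measured has not changed. Here the only two scores described lie on either side of a 12-week programme for half the sample, and the same pair is used to look for an effect of that programme. If people respond to PAIL to different degrees, their rank order shifts for a real reason and the correlation drops. A low value could then mean a noisy scale or a varied response, and the coefficient could not say which.

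The Study objectives list the appropriateness of the assessment tools as an aim. This coefficient is the only check of reliability that the article plans for a scale it has altered. At stake is how far that one number can be interpreted when tools are chosen for the main trial.

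**Working it through.** The article derives no figure of its own for this analysis. The 0.78 is cited from previous research and cannot be reproduced here. What follows is an illustration.

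**Inputs from the protocol article**
- Reliability R = 0.78 (Questionnaires).
- 20 participants per arm, 40 in total (Sample size).
- Lowest retention that meets the progression criterion: 75% per group, so 0.75 × 20 = 15 per arm (Progression criteria).
- No intervention in the wait-list arm before its follow-up measures (WLC group).

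**Assumed inputs, not in the article**
- Mean response to PAIL d = 0.5 baseline SD.
- SD of individual response s = 0, 0.5 or 1.0 baseline SD, independent of the baseline score.

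**Model.** Each score is a true score plus error, with baseline variance 1 and true-score variance 0.78. In the intervention arm the second score gains a response with mean d and SD s. The covariance between the two scores stays at 0.78. The pooled variance of the second score is 1 + s²/2 + d²/4: half the sample has the extra variance s², and the gap between the arm means adds d²/4.

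**Pooled correlation** = 0.78 / √(1 + s²/2 + d²/4)
- d = 0.5, s = 0: 0.78 / √1.0625 = 0.757
- d = 0.5, s = 0.5: 0.78 / √1.1875 = 0.716
- d = 0.5, s = 1.0: 0.78 / √1.5625 = 0.624

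**Intervention arm alone** = 0.78 / √(1 + s²)
- s = 0: 0.78, because a uniform shift does not alter a within-arm correlation
- s = 0.5: 0.78 / √1.25 = 0.698
- s = 1.0: 0.78 / √2 = 0.552

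**Wait-list arm alone** = 0.78 × (12-week stability of the true score)
- stability 1.0: 0.78
- stability 0.9, 0.8, 0.7 (assumed): 0.70, 0.62, 0.55

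**Precision.** The 95% interval is tanh(atanh(r) ± 1.96/√(n − 3)), with atanh(0.78) = 1.045. It is exact for neither an ICC nor samples this small, but it gives the scale.
- n = 40: 0.62 to 0.88
- n = 20: 0.52 to 0.91
- n = 15: 0.45 to 0.92

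**The case against.** **The time points and arm are not stated.** A reader might infer that the article commits to a pooled baseline-to-week-12 correlation. It does not say so. The visit chart (Fig. 1) is not shown, and the article mentions that "potential participants will be offered a total of five visits for health assessments at the university facility" without itemising them. This stands as a caveat. Even so, Measures allows only two occasions and no short-interval retest is described. The next sentence of the analysis section confines a different set of correlations to the experimental group, so the article does name a subset when it intends one. If a short retest exists, stating it would settle the main point.

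**The intervention lies between the scores in one arm only.** This is correct. It is also why a sound subset is available at no cost.

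**The loss may be small.** A reader might infer that a sound scale will look unreliable. The figures do not establish that. With a uniform response the pooled value is 0.757, close to 0.78. The larger losses need variation in response that the article gives no evidence for. Both 0.716 and 0.624 lie within the interval around 0.78 at n = 40. What remains is a problem of interpretation: the source of a low value could not be identified.

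**A mean shift would not be hidden.** A correlation ignores a shift common to everyone, but the planned group-by-time ANOVA on the same scale would show it. The choice of an ICC is therefore a refinement, secondary to the choice of arm.

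**The shortened scale.** A reader might infer that removing four items has lowered internal consistency by a calculable amount. The article does not give the number of items or say which sub-scale each quoted coefficient belongs to, and it already attributes those coefficients to previous research. No figure can be supported.

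**Consequence.** No reliability threshold is set, the analysis is described as additional, and progression rests on safety, recruitment and retention. This stands and keeps the point minor.

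**Conclusion.** The point holds, as a minor one. As described, the plan offers only two scores per person, about 12 weeks apart, with PAIL between them in the intervention arm, and it does not keep that arm out of the reliability calculation. Including it would lower a true 0.78 to somewhere between about 0.76 and 0.62 when the arms are pooled, depending on how unevenly people respond. That range rests on an assumed mean response of 0.5 SD, an assumed response SD of 0 to 1.0, and response unrelated to baseline. If response depended on baseline, the size of the bias, and possibly its direction, would differ, but the coefficient would still not isolate reliability. The documents do not support a claim that the scale would be wrongly dropped or kept, or that the decision to proceed to a main trial is affected.

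**What to change.** In the Quantitative data analysis section, state that the coefficient is computed in the wait-list arm only, from baseline to the 12-week follow-up, as an absolute-agreement ICC with a 95% confidence interval. Report it as 12-week stability rather than as pure test-retest reliability. If a separate short-interval retest is in fact planned, describe that instead.

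The change is one of wording and needs no new data. Its costs are these:
- **Precision.** The analysis uses about 20 people rather than 40. Around 0.78 the interval is about 0.52 to 0.91, or 0.45 to 0.92 with 15 people, wide enough to contain both 0.72 and 0.62.
- **Natural change.** True scores may drift over 12 weeks without any intervention. A true-score stability of 0.9 would by itself bring the value to 0.70, so a low result would still need careful reading.

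As an optional extra, Cronbach's alpha for the shortened expected outcomes sub-scale can be calculated from the baseline scores of all participants, before any intervention, with no additional data.

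### Change-score correlations in the intervention arm alone cannot show which outcome suits the main trial, and the planned test-retest correlation appears to span the intervention

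*Protocol article*

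**What the plan says.** **Outcome choice.** Identifying the best primary outcome for the main trial is one of the aims under Study objectives. In Quantitative data analysis, one analysis is introduced with that purpose: "In order to explore which outcome measures are likely to be the most important for the main trial", Pearson "correlations will be performed between calculated change scores over time in the experimental group for all psychosocial outcomes". The psychosocial side is then spelled out as "Lubben’s social networks, loneliness and self-efficacy for exercise". The activity side is "time lying/sitting (h), time standing (h), time stepping (h), step counts, sit-to-stand transitions (n) and energy equivalent (METs/h").

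**Retest.** For the Expected Outcomes and Barriers for Habitual Exercise scale, the same section says that "additional test-retest reliability will be calculated via correlation". It gives no interval, arm or type of coefficient. Measures places every assessment except the focus groups at baseline and immediately after the intervention. Data collection agrees: "Data will be collected at the university facility at screening, baseline and post-intervention period (12 weeks after the start of the intervention"). Questionnaires reports that "Four questions related to sport competence have been deleted from the expected outcomes sub-scale" and cites a test-retest reliability of 0.78 from earlier research. Feasibility outcomes and Quantitative data analysis also treat this scale as an outcome to be compared between arms.

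**The concern.** The main-trial hypothesis in Background is a greater fall in loneliness than in the control group. An outcome suits that trial if it can be measured well and moves relative to control. A correlation between two changes inside one arm addresses neither. At most it bears on whether people whose activity rose more also changed more psychosocially. Read as a ranking, it favours measures that track activity, although Background also proposes routes through group identification and social support.

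The list contradicts its own label. The text promises all psychosocial outcomes and names three. Social support is missing, yet the next sentence offers it, alongside loneliness, as an example for the main-trial power calculation, and Feasibility outcomes calls it a potential primary outcome. An analysis that leaves out a candidate cannot inform the choice of it.

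The retest correlation raises a different problem. If its two time points are baseline and week 12, the same pair of scores is used to estimate the scale's stability and the intervention's effect on it. A sound scale could then look unreliable because participants truly changed.

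**Working it through.** **Inputs**
- Arm size: 20 per arm (Sample size). The 75% retention floor per group (Progression criteria) gives 0.75 × 20 = 15.
- Correlations: 3 psychosocial × 6 activity measures = 18.
- Significance level: 0.05 (Quantitative data analysis), taken as two-sided.
- Cited retest reliability: 0.78 (Questionnaires).
- The protocol gives no precision figure for either analysis, so there is none to reproduce.

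**1. What the change-score correlation measures.** Adding a constant to everyone's change leaves Pearson's r unchanged, so an average effect shared by the arm drops out. A simulation with large samples shows both extremes:

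| Within-arm r | Between-arm effect |
|---|---|
| 0.50 | about 0 |
| about 0 | about -0.80 SD |

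**2. Precision.** Critical r = t / √(t² + n − 2). The 95% CI is tanh(atanh r ± 1.96/√(n − 3)).

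| n | Critical r | 95% CI for r = 0.3 |
|---|---|---|
| 20 | 0.44 | -0.16 to 0.66 |
| 15 | 0.51 | -0.25 to 0.70 |

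At n = 15: atanh 0.3 = 0.310 and 1.96/√12 = 0.566, so the limits are tanh(-0.256) = -0.25 and tanh(0.875) = 0.70.

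If no true associations exist, 18 × 0.05 = 0.9 nominally significant results are expected. The chance of at least one is 1 − 0.95^18 = 0.60 if the tests are independent, which they are not.

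**3. The list.** Quantitative data analysis names seven psychosocial outcomes for the ANOVAs: loneliness, social support, support networks, depression, anxiety, self-efficacy and satisfaction with contacts. The correlations name three. The four left out are social support, depression, anxiety and satisfaction with contacts.

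**4. Retest across the intervention.** Take 0.78 as the true reliability (unit observed variance at baseline, true-score variance 0.78). Let individual true change have SD equal to s times the true-score SD. Then r = 0.78 / √(1 + 0.78 s²). The values of s are assumptions; the documents give none.

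| s | Pre-post r |
|---|---|
| 0.25 | 0.76 |
| 0.5 | 0.71 |
| 0.75 | 0.65 |
| 1.0 | 0.58 |

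A uniform shift of d SD in one arm leaves that arm's r at 0.78. With equal arms pooled, r = 0.78 / √(1 + d²/4), which is 0.76 at d = 0.5 and 0.72 at d = 0.8. Within an arm, then, Pearson's r falls with uneven true change and does not register a uniform shift.

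**5. Cost of using the wait-list arm alone.** By the same Fisher formula, a coefficient of 0.78 has a 95% CI of 0.52 to 0.91 at n = 20 and 0.45 to 0.92 at n = 15. Pooling both arms (n = 40) would give 0.62 to 0.88. These are Pearson intervals, used as a guide to the width for an ICC.

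**The case against.** The strongest reply is that these correlations are not the selection rule. The text says they explore, and warns that hypothesis testing is preliminary, underpowered and to be read with caution. Other planned information bears on outcome choice: effect sizes and group-by-time ANOVAs across both arms, questionnaire completion, focus groups, and power calculations from between-group mean differences. Background's secondary hypothesis also links rising activity to psychosocial gains, and a change-change correlation is a natural first look at that.

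All of this stands. A reader might infer that the control arm is ignored, or that the aims on outcome choice and assessment tools would be answered by noise. The documents do not support that: the restriction to one arm applies to this analysis, not to the whole plan. The warning about small numbers does not, however, repair an analysis that measures something other than its stated purpose, and it does not put social support back on the list.

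On the retest, a reader might take it as settled that the pair is baseline and week 12. No sentence says so. Data collection mentions five visits, and the visit chart is not available here, so a short-interval retest cannot be excluded. The article may also leave such detail to a fuller document. What stands is that the text describes only two administrations of the scale. In the wait-list arm the correlation would be a legitimate long-interval stability estimate, so it would be too strong to say that the analysis cannot work. The deletion of four items is disclosed and is not itself an error.

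**Conclusion.** The point holds in limited form.

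- **Outcome choice:** firm. The restriction to the experimental arm is explicit, and such correlations cannot show which outcome moves relative to control. At 15 to 20 people they are also too imprecise to rank measures.
- **The list:** firm. It names three of seven outcomes and omits a named candidate.
- **Retest:** conditional. If the pair is baseline and week 12, as the described schedule suggests, the intervention-arm coefficient confounds unreliability with true change. The loss is small (0.78 to 0.76) or substantial (0.78 to 0.58) depending on an assumed spread of true change.

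The 60% chance of a false positive should not be quoted as this plan's error rate. It assumes 18 independent tests, whereas step counts, stepping time and energy expenditure overlap.

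Neither analysis affects the progression criteria or the between-arm estimates.

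**What to change.** **Outcome choice.** Keep the correlations as descriptive results with confidence intervals, for all seven psychosocial outcomes (7 × 6 = 42 with the present activity measures), and do not tie them to the choice of outcome. Base that choice on information already planned in both arms, for every candidate including social support: the between-arm difference with its CI, completion rate and focus-group acceptability. The between-arm difference should not become a largest-effect rule either. In SD units its 95% half-width is roughly 1.96 × √(2/20) = 0.62 at 20 per arm.

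**Retest.** State the interval, arm and coefficient. If only baseline and week 12 exist, use the wait-list arm alone, with an absolute-agreement ICC and CI labelled 12-week stability. Report baseline Cronbach's alpha of the adapted scale in all participants. If a short-interval retest is scheduled, state its interval and use that instead.

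**Cost.** Only the analysis wording changes and no new data are needed. The price is the wide interval from using the wait-list arm alone, about 0.52 to 0.91 for a coefficient of 0.78 at n = 20.
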